### **12.1 Analysis datasets**

#### **● Modified Intention-to-treat (mITT)**

The mITT population is defined as all randomized subjects who received open surgery or laparoscopic surgery. The modified intention-to-treat (mITT) population will serve as the primary population for efficacy analyses in this study.

#### **● Per-protocol set (PPS):**

The PPS includes patients who meet the inclusion criteria, do not meet the exclusion criteria, and complete the treatment plan. In other words, the participants who meet the trial plan, have good compliance, and complete the items specified in the eCRF are included in the per-protocol (PP) analysis. PP analysis is mainly applied to the primary outcome measure.

#### **● Safety Set (SS):**

The SS includes the actual data of participants who have received treatment and have records of safety indicators. The missing data of safety indicators cannot be obtained from carry-over from previous records. The dataset includes some patients excluded from the trial, e.g., those whose age exceeds the inclusion criteria. However, it excludes the patients who have used prohibited drugs that interfere with the safety evaluation. The incidence of adverse reactions is determined by using the number of cases in the SS as a denominator.

### **12.2 Statistical methods**

#### **(1) Case enrollment analysis**

- The number of patients, the number of enrolled patients, and the number of patients who complete the trial in each center are listed to generate three analysis datasets (FAS, PPS, and SS).
- The patients who drop out and are excluded are listed, along with the reasons.

## **(2) Demographic data and baseline analysis**

- Descriptive statistical, demographic data, and other baseline characteristic values:
  - The number of cases, mean, standard deviation, median, minimum, and maximum, are calculated for continuous variables.
  - The frequency and composition ratios are calculated for the continuous and categorical data.
  - The inferential statistical results (*P* values) are given as descriptive results.

## **(3) Outcome analysis**

### **Analysis of primary outcome measures**

- The DFS is calculated using the Kaplan-Meier method after the last participant has been enrolled for three years. The median DFS time and its 95% confidence interval are compared between the two groups using the log-rank test. Cox regression is used to calculate the hazard ratio and its one-sided 95% confidence interval between the two groups. According to the preset noninferiority criteria, the inferiority of the treatment to be tested compared with the control treatment is determined.

### **Analysis of secondary outcome measures**

- Pathologic outcomes, including the TME quality, negative CRM, and negative DRM, are presented as numbers (percentage) and compared using the Chi-square test.
- The operation time (min) and estimated blood loss (ml) are compared between the groups by the Wilcoxon method.
- The OS is calculated using the Kaplan-Meier method after the last participant has been enrolled for three years. The median OS time and its 95% confidence interval are compared between the two groups using the log-rank test.
- The OS when the last participant is enrolled for five years is determined by using the Kaplan-Meier method. The median OS time and its 95% confidence interval are compared between the two groups using the log-rank test.
- Time to tumor recurrence is determined using the Kaplan-Meier method. The median time of recurrence and its 95% confidence interval are compared between the two groups using the log-rank test.
- The perioperative recovery time is compared between the groups using the Wilcoxon method.
- The length of postoperative hospital stay (d) is compared between the groups using the Wilcoxon method.
- The incidence of intraoperative complications is compared between the groups by the  $\chi^2$  test or Fisher's exact probability method.
- After surgery, the incidence of complications and 30-day mortality rate are compared using the  $\chi^2$  test or the Fisher's exact tests for probability.

## **(4) Safety analysis**

- The incidences of adverse events and adverse reactions are calculated.

- The frequency and number of adverse events and reactions in different organ systems are recorded, from which the percentage of adverse events/reactions in each system is obtained.
- A detailed list of all adverse event cases is provided.
- A detailed list of all adverse reaction cases is provided.
- The number and percentage of patients whose laboratory tests, ECG, and physical examination results have changed from average to abnormal or show deteriorated abnormalities after the trial are calculated.
- Patients having abnormal laboratory test results, ECG, and physical examination results are listed, along with the clinical explanations.

### **12.3 Statistical software and general requirements**

- SAS 9.4 is used for analysis
- Generally, two-sided tests are used for statistical analysis, and a  $P$  value  $< 0.05$  indicates that the difference is statistically significant.

## **13. On-site inspection**

All participating hospitals are subject to on-site inspection twice a year by the contract research structure (CRO). The items to be inspected/methods of inspection include:

- Quality of the eCRF records
- Interviewing participants
- All participating hospitals must cooperate with the clinical research quality inspector and provide necessary convenience.

### **15. Ethical rules of this study**

#### **15.1 Ethical principles**

The study plan is designed and implemented following the relevant provisions of the Declaration of Helsinki to protect the rights and interests of all participants.

#### **15.2 Ethical review process**

The study plan is chosen by the principal investigator and the sponsor through discussion and is implemented after the ethics committee grants approval before the beginning of the trial.

#### **15.3 Responses to ethical review decisions**

After necessary revision, the ethics committee may approve, disapprove the study plan, and terminate/suspend the trial after it has been approved. The research team will revise the plan according to the ethical review comments and implement it according to the final approved plan.

#### **15.4 Registration of this study**

Before its beginning, the study was registered at ClinicalTrials.gov with registration number NCT01899547.

#### **15.5 Privacy protection of participants**

Investigators must ensure the privacy of participants. Participants' names and patient numbers shall not appear in the documents submitted to the sponsor, in which their trial identity number can only represent the participants. Investigators must keep the enrollment

form meticulously with the participants' names and addresses corresponding to trial identity numbers.

## **15.6 Modification of the study plan**

After the ethics committee approves the study plan, significant modifications can be made during the trial process only after an "Explanation of the Modifications to the Study Plan" is written and signed by the principal investigator of the organization study and is approved by the ethics committee. Nonfundamental modifications can be made after the principal investigator, statistician, and methodologist of the organization in charge of the study discuss and sign the modification form.

## **16. Adverse events**

### **16.1 Definitions of adverse events**

Adverse events refer to any medical phenomena when participants are treated with different surgical procedures or adjuvant chemoradiotherapy regardless of whether the phenomena are causally related to the treatment. This term also covers laboratory test results or other diagnostic procedures considered clinically relevant (e.g., those requiring unscheduled diagnostic procedures or treatment or resulting in withdrawal from the study).

#### **Adverse events may include:**

- The symptoms or disease signs or accompanying symptoms deteriorate under treatment
- The treatment efficacy is affected, which may be related to the research procedures
- Any combination of the factors above

Hospitalization before inclusion in the study will not be considered an adverse event. Such criteria are also suitable for patients hospitalized for less than 12 hours; part of the regular treatment or monitoring of the disease to be studied, or the patient is hospitalized not because of deterioration of the disease.

#### **An adverse event is considered to have a severe consequence if it:**

- Leads to death
- Is life-threatening
- Requires hospitalization or prolongs hospitalization (the exceptions are listed below)
- Causes permanent or severe disability or incapacity to work
- It is a significant medical event

### **Death:**

If death results from treatment, the cause of death should be considered a serious adverse event. Death resulting from tumor development itself is not included.

An exception to this rule is "sudden death" without a clear cause. In this case, sudden death should be regarded as an adverse event and "fatal" as the cause of being "serious."

### **Life-threatening:**

An adverse event is defined as "serious." "Life threat" refers to adverse events in which a participant is at risk of death due to treatment. It does not refer to adverse events that, if more serious, may lead to the hypothesis of death.

### **Hospitalization:**

Any treatment-related adverse reaction that leads to hospitalization or prolongation of hospitalization is automatically considered serious except for these situations: the hospital stay is shorter than 12 hours, the hospitalization is planned before the beginning of the study (e.g., elective or planned surgery before the beginning of the study), or hospitalization is not related to adverse events (e.g., admission to a social welfare medical institution for short-term care).

During hospitalization, any interventional treatment may meet the criteria of medical importance and, therefore, may be reported as a severe adverse event based on clinical judgment. In addition, when local regulatory authorities explicitly require stricter definitions, local regulations are judged by precedent.

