## **16.5 Reporting of adverse events**

- For any serious adverse event or unexpected adverse event, the investigator must report the event to the Research Committee/PI ([name]), the ethics committee responsible for dealing with serious adverse events, and the local personnel in charge of medical safety management within 24 hours after knowing of the adverse event, regardless whether the event is related to the treatment.
- The outcomes (regression, death, etc.) of serious adverse events that have been reported will be followed up and recorded. According to the national regulations, the study's organization reports the data to the relevant authorities. In any case, all personnel of the study must comply with local legal provisions and requirements.

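### Protocol section 16.1 defines seriousness first by outcome and then by cause, so an expected event judged unrelated can miss both the 24-hour report and the SAE row of SAP Table 13

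*Combined protocol and SAP*

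**What the plan says.** Protocol section 16.1 defines an adverse event "regardless of whether the phenomena are causally related to the treatment". It then lists five outcomes that give an event a severe consequence. None carries a causal condition. The hospitalization item reads "Requires hospitalization or prolongs hospitalization (the exceptions are listed below", followed by a closing bracket. The list serves as the seriousness test, because the paragraphs after it explain its items one by one.

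Those paragraphs add a causal element:

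- Death: "If death results from treatment, the cause of death should be considered a serious adverse event". Tumour deaths are set aside ("Death resulting from tumor development itself is not included"). For an unexplained sudden death, "sudden death should be regarded as an adverse event", and it is classed as serious.
- Life-threatening: "adverse events in which a participant is at risk of death due to treatment".
- Hospitalization: "Any treatment-related adverse reaction that leads to hospitalization or prolongation of hospitalization is automatically considered serious", with exceptions for stays under 12 hours, admissions planned before the study, and admissions that do not stem from an adverse event.
- Disability: loss of the ability to live normally, caused by treatment.
- Significant medical events: treatment-related events that may be classed as severe.

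Section 16.4 has the investigator record each event's relationship to treatment as a separate item. Section 16.5 requires a 24-hour report of any serious or unexpected event, "regardless whether the event is related to the treatment". SAP Table 13 compares the number and percentage of patients with an SAE between arms, with a P value, in the safety set. The SAP spells out the abbreviation SAE but does not define it.

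**The concern.** Seriousness describes what happened to the patient, and relatedness describes why. Section 16.5 depends on keeping them apart: a duty to report serious events whether related or not has content only if an unrelated event can be serious. The criterion paragraphs merge the two and leave a site without a clear rule.

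Two things are at stake. Some serious events judged unrelated might not reach the principal investigator and the ethics committee within 24 hours. And the SAE row of Table 13 would count, at least in part, what investigators chose to attribute to treatment. Protocol section 11.1.9 confirms that the trial is open-label, so that judgement is made knowing which operation the patient had. If attribution differs by arm, the row can differ with no difference in harm.

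**Working it through.** The plan states no figure on this point, so the check is a comparison of texts.

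**Step 1: is causation part of seriousness?**

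| Place in protocol | Causal condition? |
|---|---|
| 16.1, adverse event definition | No, expressly excluded |
| 16.1, list of five outcomes | No |
| 16.1, Death | Yes, except unexplained sudden death |
| 16.1, Life-threatening | Yes, within the definition |
| 16.1, Hospitalization | Yes, in the sentence that makes events automatically serious |
| 16.1, Disability | Yes, within the definition |
| 16.1, Significant medical events | Yes, but permissively worded |
| 16.5, 24-hour report | No, expressly excluded |

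The conflict that matters is between the five paragraphs on one side and the list and 16.5 on the other. The cause-neutral definition of an adverse event is weaker evidence, since it could coexist with a narrower SAE definition.

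**Step 2: can an event escape the 24-hour report?** Section 16.5 has two routes, serious or unexpected. Section 16.2 lists pneumonia and cardiovascular and cerebrovascular events, including thrombosis and embolism, among the expected operation-related events. Take a non-fatal readmission for one of these that the investigator judges unrelated. It is not unexpected. Under the Hospitalization paragraph read narrowly, it is not serious either. Neither route then requires the report.

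**Step 3: what happens in the SAP?** The same event stays in the adverse-event row of Table 13 but is missing from the SAE row.

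**Step 4: what still captures it?** Protocol 8.4.4 counts any complication within 30 days, and SAP Table 6 has rows for cardiovascular events and pneumonia. Protocol 8.4.5 counts 30-day deaths from any cause. DFS counts recurrence or death. None of these needs attribution. After day 30, including during adjuvant therapy, the 30-day endpoints no longer capture a non-fatal event.

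**Step 5: illustration only.** The documents give no SAE rate and no share judged related, so every input here except the arm sizes is an assumption. Let the true all-cause SAE rate r be equal in both arms and let shares a1 and a2 be judged related. The row then shows r × a1 and r × a2. With r = 15%, shares of 80% and 70% give 0.15 × 0.80 = 12.0% and 0.15 × 0.70 = 10.5%, a gap of 1.5 points from attribution alone. Using the planned arms (646 laparoscopic, 322 open), with the higher share placed arbitrarily in the laparoscopic arm, the chance of a significant result in that direction in a two-sided 5% test of proportions is:

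| Shares judged related | r = 10% | r = 15% | r = 20% |
|---|---|---|---|
| 80% vs 70% | 7.5% | 9.7% | 12.1% |
| 80% vs 60% | 19.1% | 28.1% | 37.6% |
| 90% vs 60% | 35.9% | 53.0% | 67.9% |

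With equal shares, the chance in one direction is 5% / 2 = 2.5%. The table shows how the row would behave under the narrow reading. It does not estimate what will happen.

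**The case against.** A reader might infer that an unrelated event can never be serious, so that the reporting rule in 16.5 cannot work. The documents do not support that:

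- The list of outcomes is the only general test. It has no causal condition, and nothing says the later paragraphs override it.
- The Hospitalization sentence says which events are automatically serious. Read literally, that is a sufficient condition and does not rule out others. Its third exception concerns admissions not arising from an adverse event, which is different from events unrelated to treatment.
- The same paragraph lets in-hospital interventions be reported on clinical judgement and gives way to stricter local definitions.
- Unexplained sudden death counts without attribution, and the paragraph on significant medical events is permissive.
- Unexpected events must be reported under 16.5 regardless of seriousness.

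All of this stands, and it limits the point to expected events at sites that follow the narrower wording. It does not remove the contradiction. The Life-threatening and Disability paragraphs are definitions, with causation inside them, so the sufficient-condition argument does not reach them. For hospitalization, the list sends the reader to the paragraph below, which speaks only of treatment-related reactions.

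It can also be said that 16.2 gives one list of operation-related events for both arms, which makes a judgement of unrelated less likely. That is fair, but 16.4 still asks the investigator to judge each event. Finally, the SAE rate is not among the primary, secondary or other outcomes in protocol section 8, and Table 13 does not itself limit its SAE row to related events. Both are true. They reduce the importance of the point and also show that the SAP leaves the definition open.

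**Conclusion.** The contradiction within 16.1, and between 16.1 and 16.5, is real and can be read from the text alone. A site applying the criterion paragraphs can leave an expected, non-fatal event that it judges unrelated out of both the 24-hour report and the SAE row of Table 13. Under that reading, the row depends partly on open-label attribution.

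This rests on one assumption, that at least some sites, or the programming of Table 13, follow the criterion paragraphs and not the outcome list. The documents do not say which governs. The size of the effect is unknown. The figures above are illustrations, and no share of unreported SAEs can be stated. The documents also give no basis for predicting which arm would be favoured, or that attribution will differ at all.

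It would go too far to infer that the trial's main safety or efficacy results are compromised. DFS, 30-day complications and 30-day any-cause mortality do not pass through these definitions. The wording should be corrected for the sake of reporting and a clear SAE row.

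**What to change.** 1. In protocol 16.1, reword the paragraphs on death, life threat, hospitalization, disability and significant medical events so that seriousness follows the listed outcomes with no causal condition. Keep the stated exceptions for tumour death, stays under 12 hours and planned admissions. The tumour-death exception still needs a judgement of cause, so some attribution remains for deaths, but 30-day mortality, DFS and overall survival count deaths from any cause.
2. Keep relatedness as the separate item that 16.4 already requires.
3. In the SAP, state that the SAE row of Table 13 counts all-cause SAEs under that definition, and add a second line for treatment-related SAEs.

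The cost is a wording change and one table row. Treatment, sample size and the primary analysis do not change. The downside is more SAE reports and a higher reported SAE rate in both arms.

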### **Disability:**

Disability refers to the substantial destruction of a person's ability to live a normal life due to treatment.

### **Significant medical events:**

Any treatment-related adverse event can be considered severe because it may endanger the participant and require interventions to prevent another difficult situation from occurring. A significant medical event may be indicative of a seriously ill state. Therefore, it is essential to ensure that special attention is paid to reporting significant medical events, which might be more critical than the reports on other issues.

## **16.2 Expected adverse events**

### **Operation-related adverse events:**

The complications specific to laparoscopic surgery include subcutaneous emphysema, hypercapnia, vascular and gastrointestinal injuries associated with a puncture, and gas embolism.

The common complications of laparoscopic surgery and open surgery mainly include:

- 1) Presacral hemorrhage
- 2) Anastomotic leakage
- 3) Anastomotic bleeding
- 4) Active intra-abdominal bleeding
- 5) Intestinal adhesion and intestinal obstruction
- 6) Internal hernia
- 7) Injuries to the surrounding organs, including the ureter and duodenum
- 8) Intestinal fistula and lymphatic leakage
- 9) Urination disorder and sexual dysfunction
- 10) Difficulty in bowel movement or frequent bowel movements
- 11) Complications of colostomy
- 12) Incision complications (infection, effusion, dehiscence, poor healing, etc.)
- 13) Pneumonia, urinary tract infection, renal failure, liver failure, cardiovascular and cerebrovascular events (including thrombosis, embolism, etc.)
- 14) Others.

### **Adverse events caused by deterioration of the primary disease:**

Adverse events related to various forms of deterioration of the primary disease are recorded according to the “Short Name” in Common Terminology Criteria for Adverse Events (CTCAE) v4.0. They include:

- 1) Adverse events caused by primary lesions and peritoneal disseminated lesions:

Gastrointestinal tract: loss of appetite, constipation, dehydration, abdominal fullness, heartburn, nausea, gastrointestinal obstruction [stomach, duodenum, ileum, colon, and small intestine (not subdivided)], gastrointestinal perforation (stomach, duodenum, jejunum, ileum, and colon), gastrointestinal stenosis (stomach, duodenum, jejunum, ileum, and colon), vomiting, hyponatremia, gastrointestinal bleeding (stomach, duodenum, jejunum, ileum, and colon)

- 2) Adverse events caused by liver metastasis:

Abnormal metabolic/clinical examination results: aspartate aminotransferase (AST), alanine aminotransferase (ALT), bilirubin, and alkaline phosphatase

- 3) Adverse events caused by lung metastasis:

Lung/upper respiratory tract: atelectasis, dyspnea, hypoxemia, and airway occlusion (bronchi)

- 4) Adverse events caused by other metastatic lesions:

Pain: pain (metastasis sites) and hypercalcemia

5) Adverse events related to the deterioration of general condition:

- General conditions: fatigue, weight loss, and cachexia
- Blood/bone marrow: abnormal hemoglobin and platelet levels
- Cardiovascular system: hypotension
- Lymphatic system: edema in the head and neck, limbs, body trunk/genitals, and viscera
- Metabolism/clinical test results: hypoproteinemia, AST, ALT, acidosis, creatinine, hyperglycemia, hypoglycemia, hypernatremia, hyponatremia, hyperkalemia, hypokalemia, and other electrolyte disorders
- Lung/ upper respiratory tract: pleural effusion (nonmalignant), dyspnea, hypoxemia, and lung infection
- Genitourinary organs: cystitis, renal failure, and oliguria/anuria

